## Radiological response definitions

### Target lesions

- Complete response (CR): disappearance of all target lesions.
- Partial response (PR): At least a 30% decrease in the sum of the longest diameter of target lesions taking as reference the baseline sum.
- Stable disease (SD): Neither sufficient shrinkage to qualify for partial response nor sufficient increase to qualify for progressive disease taking as reference the smallest sum of the longest diameter of target lesions since the treatment started.
- Progressive disease (PD): At least a 20% increase in the sum of the longest diameter of target lesions taking as reference the smallest sum of diameter for all target lesions recorded since the treatment started.

### Evaluation of non-target lesions and new lesions

- Complete response (CR): disappearance of all non-target lesions.
- Incomplete response/stable disease: the persistence of one or more non-target lesion(s)
- Progressive disease (PD): unequivocal progression of existing non-target lesions and/or the appearance of one or more new lesions.

### Evaluation of best overall response

The best overall response is the best response recorded since the start of treatment until disease progression or recurrence, taking as reference for progressive disease the smallest measurements recorded since the treatment started. Table 1 below provides overall responses for all possible combinations of tumor responses in target and non-target lesions, with or without the appearance of new lesions.

Table 1

Target lesions Non-target lesions New lesions Overall response

CR CR No CR

CR Incomplete response/SD No PR

PR Non-PD No PR

SD Non-PD No SD

PD Any Yes or no PD

Any PD Yes or no PD

Any Any Yes PD

### Response confirmation

CR, PR and SD must be confirmed by a complete tumor staging performed no less than 4 weeks (usually at the next scheduled 6 week interval evaluation) after the criteria for response are first met (normally at the next preplanned evaluations).

## Duration of response and survival

The duration of response (CR or PR) will be calculated from the time point a PR or CR has been documented until the documentation of progression.

The time to progression (TTP) will be calculated from the date of recruitment to the study until the documentation of progression, the latest date of follow up for patients who are lost to follow-up or the date of death.

Overall survival will be calculated from the date of recruitment to the study until the date of death or latest date of follow up for patients who are lost to follow-up.

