# Protocol synopsis

| **Title**  PROSPECTIVE EVALUATION OF SMALL MOLECULE EGFR-1 TYROSINE KINASE INHIBITION AS A FIRST-LINE TREATMENT IN PATIENTS WITH ADVANCED NON-SMALL CELL LUNG CANCER (NSCLC) HARBOURING A MUTANT EGFR GENE |
| --- |
| **Sponsor / Study Coordination**  Dienst Medische Oncologie - Oncologisch Centrum  Academisch Ziekenhuis Vrije Universiteit Brussel |
| **Study hypothesis**  Erlotinib is a safe and effective first-line treatment for NSCLC harboring a mutant EGFR |
| **Study design**  One arm, multicenter investigator initiated phase II study. |
| **Primary objective**  To investigate the efficacy and feasibility of using a small molecule EGFR inhibition in the first-line treatment of non-small cell lung cancer carrying (a) EGFR kinase domain mutation(s) not amenable to curative treatment. |
| **Primary endpoint**  Progression free survival time. |
| **Secondary objectives**  Objective response rate according to the RECIST criteria, metabolic response rate Feasibility, toxicity, duration of response and survival (TTP and OS from the date of study entry). |
| **Secondary endpoints**   - Toxicity according to the NCI-CTCAEv3 criteria. - Feasibility (reported descriptively). - Duration of response - Overall survival (from the initiation till PD). |
| **Patient selection criteria**   - - **Identification of an EGFR TKD mutation in the tumor material of the patient.** - No previous chemotherapy for metastatic disease. - Patients in whom any other anticancer treatment is needed after inclusion in the study will be considered to have met the primary endpoint. - Standard phase II recruitment criteria. |

| **Treatment plan and special procedures**  Patients will remain in the study under continuous treatment with erlotinib as long as they remain progression free, receive no other secondary anticancer treatment and remain free from unacceptable toxicity. |
| --- |
| **Study treatment duration, discontinuation and study withdrawal**   - At any time during study, progression of disease, unacceptable toxicity or patient refusal will result in study treatment discontinuation. - Patients that stop study treatment for other reasons than progressive disease must be followed by serial assessment of their response status as provided by the protocol |

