### Baseline evaluation, during which the mutation screen is being performed.

### Evaluation of eligibility.

### Inclusion and treatment.

### Response assessments (imaging and physical) and ancillary parameters at 6, 12, 18 and 24 weeks. Thereafter every 12 weeks until disease progression (RECIST definition). A first metabolic response assessment will be at 2 weeks and subsequently synchronized with the radiological evaluations. A concomitant CT-scan at 2 weeks is recommended.

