### Time to Progression

The Time to Progression is defined as the time from start of treatment to the date of the first documented progression (according to RECIST criteria) or the date of death for any reason in the absence of PD. Patients who have not died or progressed at the time of the final analysis will be censored at the date of last contact.

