### Survival Assessment

Overall survival will be determined from the date of start of treatment to the date of death irrespective of the cause of death. At the end of the study a survival follow up report for each patient is required. Patients who have not died at the time of the final analysis will be censored at the date of last contact.

Time to progression and survival will be summarized using Kaplan-Meier methodology.

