Survival (time to progression and overall survival) will be calculated from the start of therapy until disease progression or death or last follow-up according to the Kaplan-Meier method with SPSS statistical software (release 7.5, 1996; SPSS Inc, Chicago, IL).

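### Time to progression, the only working definition behind the 3-month PFS proportion, has two starting points; if recruitment precedes the first dose by more than about 7 days, progression found at week 12 counts as success

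*Protocol*

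**What the plan says.** Recruitment or study entry as origin:
- Section 9.4, opening text: "The time to progression (TTP) will be calculated from the date of recruitment to the study until the documentation of progression". The same text counts overall survival from recruitment.
- Section 3, synopsis, secondary objectives: "duration of response and survival (TTP and OS from the date of study entry".
- Section 6.2 counts overall survival, though not TTP, from study entry.

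Start of treatment as origin:
- Section 9.4, Time to Progression: "The Time to Progression is defined as the time from start of treatment to the date of the first documented progression". Death without progression is also an event here.
- Section 9.4, Survival Assessment: "Overall survival will be determined from the date of start of treatment to the date of death irrespective of the cause of death".
- Section 15: "Survival (time to progression and overall survival) will be calculated from the start of therapy until disease progression or death or last follow-up".

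The quantity being decided on is the proportion progression-free at three months (section 15). The two-stage rule asks for more than 8 of 13 patients with PFS beyond 3 months, then at least 26 of 35. Section 8 schedules "Response assessments (imaging and physical) and ancillary parameters at 6, 12, 18 and 24 weeks", and Table 4 in section 12.9 times these from treatment initiation.

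**The concern.** PFS is named as the primary endpoint but never defined as a time variable. The TTP definition that includes death is the only one that can serve for it, so a conflict about where TTP starts is also a conflict about the primary count.

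The two origins need not give the same count. The last scan before the landmark is fixed relative to first dose, and progression is dated when it is documented. Moving the origin back to recruitment adds the pre-treatment gap to every progression time without moving the scan. Progression found at week 12 can then fall after 3 months and count as success. The shift can only raise the success rate. In a single-arm trial with one go/no-go count there is no control arm in which it would cancel.

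**Working it through.** **1. The plan's own rule.** Inputs from section 15: p0 = 0.60, p1 = 0.80, α = 5%, β = 20%, continue if more than 8/13, succeed if at least 26/35. P(go | p) is the sum over x = 9 to 13 of P(X1 = x)·P(X2 ≥ 26 − x), with X1 ~ Bin(13, p) and X2 ~ Bin(22, p). At p = 0.60 this is 0.0499 and at p = 0.80 it is 0.808. The rule reproduces.

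**2. Day arithmetic.** Week 12 from first dose is day 84; 3 months is 365.25/4 = 91.3 days. From recruitment, an on-time week-12 scan falls on day 84 + gap:
- gap 7 days: day 91, not past the landmark (it would be if 3 months were read as 90 days)
- gap 8 days: day 92, past it
- gap 14 days: day 98, past it
- gap 21 days: day 105, past it

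**3. What gap the protocol allows.**
- *Short reading.* Section 8's flow puts inclusion after the mutation screen and eligibility check, and section 16.1 allows inclusion once the result is available. Section 11.2 requires the first dose within 1 week of establishing the mutation. The gap is then at most about 7 days.
- *Long reading.* The main text of section 8 ties inclusion to filing a form, and then makes eligibility for subsequent treatment depend on the mutation. The inclusion list in section 7.1 does not ask for a mutation result. Section 8 allows 3 weeks from baseline examinations to start, and Table 4 allows 3 weeks for consent. If recruitment means any of these events, the gap can reach about 21 days.

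**4. Size.** Assumptions, not protocol figures: exponential PFS from first dose, true 3-month rate 60%, all events dated at scans on days 42 and 84.
- S(42) = 0.6^(42/91.3) = 0.791
- S(84) = 0.6^(84/91.3) = 0.625
- first found progressed at week 12: 0.791 − 0.625 = 0.166

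If a share f of these crosses the landmark, the apparent rate is 0.625 + f × 0.166, which goes into the rule in step 1.

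| Origin and gap | f | Apparent rate | False go |
|---|---|---|---|
| First dose | 0 | 62.5% | 9% |
| Recruitment, gap 0-7 days, on-time scans | 0 | 62.5% | 9% |
| Recruitment, gap uniform 0-14 days | (14 − 7.3)/14 = 0.48 | 70% | about 34% |
| Recruitment, gap uniform 0-21 days | (21 − 7.3)/21 = 0.65 | 73% | about 49% |
| Recruitment, every gap at least 8 days | 1 | 79% | 77% |

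Treating gaps as whole or fractional days moves the middle rows by a point or two.

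**5. Late scans.** Even from first dose, a week-12 scan more than 7 days late falls past day 91. If gaps are uniform on 0-7 days and scan dates uniform within ±7 days (an assumed window), the share crossing is (6.7²/2)/(7 × 14) = 0.229. The apparent rate is 0.625 + 0.229 × 0.166 = 66%, with a false go of about 19%.

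**The case against.** The strongest reply is that the conflict may have no effect on the primary count. Section 15 and the formal TTP definition both use start of treatment, and under that origin an on-time week-12 progression is a failure at day 84. The synopsis attaches study entry to secondary objectives, so carrying it to the primary proportion is an inference. Under the short reading of recruitment, the two origins also give the same result for on-time scans. All of this stands. It limits the size of the point, but section 9.4 still contradicts itself, and recruitment has no date.

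A reader might infer that every patient failing between weeks 6 and 12 can become a success. The protocol does not support that: deaths are dated when they occur, and the synopsis treats a need for other anticancer treatment as meeting the primary endpoint. If 25% of events were dated at occurrence (an assumption), the 34% would fall to about 26% and the 77% to about 57%.

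A reader might also infer that the 34% to 77% figures are the trial's actual error rates. They are conditional on a gap that the protocol does not give.

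Finally, section 15 offers the two-stage rule as an alternative to a one-step Fleming design. The figures apply to the two-stage rule because it is the one stated with cut-offs. An SAP could choose one origin, but the protocol would still state both.

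**Conclusion.** The contradiction is certain: TTP has two origins, each stated in two places, and overall survival has the same conflict. It bears on the primary endpoint because PFS has no other definition. The effect on the go/no-go count is conditional. It is nil for on-time scans if the first dose follows recruitment within about 7 days. It is substantial, and always towards a false go, if recruitment means consent, baseline or filing of the form before the mutation result. Under the assumptions in the working, the false-go probability runs from 9% to 77% across the gaps examined, and events dated when they occur lower the figures for gaps beyond 7 days.

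The 9% floor is not an origin effect. It arises because the 60% reference is a 3-month figure while the last scan before the landmark is at day 84. It remains after the origin is settled.

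**What to change.** 1. Use one origin, the date of the first erlotinib dose, for PFS, TTP and overall survival. Align the synopsis, section 6.2, all parts of section 9.4 and the closing paragraph of section 15.
2. In section 15, define the primary endpoint as alive without progression up to and including the week-12 assessment. Progression at that assessment is a failure whatever its calendar date. This also removes the late-scan problem for that visit.
3. State that the 60% reference is a 3-month figure and that a week-12 landmark is slightly more favourable: about 62.5% under the constant-hazard assumption, with a false go of about 9% rather than 5% under the unchanged rule.

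The cost is protocol wording, by amendment. No visit, scan or treatment rule changes.

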### Time to Progression

The Time to Progression is defined as the time from start of treatment to the date of the first documented progression (according to RECIST criteria) or the date of death for any reason in the absence of PD. Patients who have not died or progressed at the time of the final analysis will be censored at the date of last contact.

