## Concomitant Medication

- Patients who have evidence of disease progression requiring radiation therapy should discontinue protocol treatment.
- Patients should receive full supportive care per institutional standards.
- Concomitant biphosphonate use to control bone pain is permitted.
- Patients with dry eyes (an abnormal Schirmer’s test results on baseline eye exam) should be advised to use an ocular lubricant.
- Concomitant treatment with warfarin or coumarin-derivative is permitted provided increased vigilance occurs with respect to monitoring INR.
- Administration of any other anti-cancer therapy (cytotoxic, biological/immunotherapy or full dose radiotherapy) is not permitted until after disease progression is documented. After permanently discontinuing the protocol treatment, patients may be treated at the investigators discretion.
- Patients who receive protocol treatment should not receive ANY other (non-anticancer) investigational drugs until after the post-treatment assessment (at least 30 days after the final dose of protocol treatment).
- Patients who continue to wear contact lenses may have an increased risk of ocular adverse events. The decision to continue to wear contact lenses should be discussed with the patient’s treating oncologist and ophthalmologist.

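### The PFS rules conflict on patients who start other anticancer treatment, and event-free patients are censored at last contact rather than at the last tumour assessment

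*Protocol*

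**What the plan says.** The synopsis (Section 3) names the primary endpoint as "Progression free survival time". Under patient selection it adds: "Patients in whom any other anticancer treatment is needed after inclusion in the study will be considered to have met the primary endpoint". Its statistical row provides for replacing patients who drop out for reasons other than progression.

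Section 9.4, under Time to Progression, takes the event date as the "date of the first documented progression (according to RECIST criteria) or the date of death for any reason in the absence of PD". Because death counts, this is a PFS definition in substance, and the protocol gives no other. It then fixes censoring: "Patients who have not died or progressed at the time of the final analysis will be censored at the date of last contact".

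The opening of Section 9.4 ends follow-up at documented progression, "the latest date of follow up for patients who are lost to follow-up or the date of death". Section 15 says survival times, including time to progression, "will be calculated from the start of therapy until disease progression or death or last follow-up according to the Kaplan-Meier method". Neither mentions other anticancer treatment.

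On treatment itself, Section 7.3 says other anticancer therapy "is not permitted until after disease progression is documented". Its next sentence reads: "After permanently discontinuing the protocol treatment, patients may be treated at the investigators discretion". The synopsis and Sections 8 and 9.5 require tumour assessment to continue until progression in patients who stop erlotinib early.

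**The concern.** There are two separate problems.

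**What counts as an event.** Suppose a patient stops erlotinib for toxicity at week 4, starts chemotherapy, and has no progression at 3 months. The synopsis endpoint rule makes this patient a failure. Section 9.4 makes the patient progression-free, and time under chemotherapy is credited to erlotinib. The synopsis replacement rule may remove the patient from the count. The protocol does not say which rule prevails.

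**When follow-up stops.** RECIST progression is established or excluded by imaging, scheduled at weeks 6, 12, 18 and 24 and then every 12 weeks. A patient last scanned at week 6 but contacted at month 5 is held at risk and progression-free to month 5. The last-contact sentence is suitable for overall survival, where Section 9.4 uses it as well, because contact shows that a patient is alive. It does not show that the tumour has not grown.

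Both matter because this is a single-arm trial whose stated purpose is to estimate the 3-month PFS proportion and judge it against fixed thresholds. No control arm shares the error.

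**Working it through.** **1. The rules side by side, for a patient who starts other treatment before progression**

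| Place | Status of the patient |
|---|---|
| Synopsis, patient selection | Has met the primary endpoint (event) |
| Synopsis, statistical row | Possibly replaced, if regarded as a drop-out for a reason other than progression |
| Section 9.4 (both definitions) and Section 15 | Not an event; followed to progression, death or last contact/follow-up |

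Section 7.3 and the continued-assessment rules affect how often this patient occurs. They do not assign a status.

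**2. The protocol's own decision rule.** Section 15 gives a Simon minimax design: p0 = 60%, p1 = 80%, α = 5%, β = 20%; continue if more than 8 of 13 are progression-free at 3 months; success if at least 26 of 35. With b(n, x, p) the binomial probability,

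P(success | p) = Σ from x = 9 to 13 of b(13, x, p) × P[Bin(22, p) ≥ 26 − x].

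This gives 0.0499 at p = 0.60 and 0.808 at p = 0.80, so the stated design reproduces.

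**3. Weight of one patient.** 26/35 = 74.3% is success and 25/35 = 71.4% is not. The step is 1/35 = 2.9 points.

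**4. Illustration on the binary count.** Let h be the share of true 3-month failures counted as progression-free. The protocol gives no h, so the values are assumptions. At a true rate of 60%, the apparent rate is 1 − 0.4(1 − h).

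| h | Apparent rate | P(success) |
|---|---|---|
| 0 | 60% | 5.0% |
| 10% | 64% | 12.0% |
| 20% | 68% | 24.4% |

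The same can be expressed as a share of all patients. If 2.5%, 5% or 10% are failures only because they started other treatment, and Section 9.4 counts them as progression-free, the apparent rate is 62.5%, 65% or 70% and P(success) is 8.8%, 14.5% or 32.7%.

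**5. Direction of the censoring effect.** The Kaplan-Meier estimate is a product of factors 1 − d/n over event times. Moving a censoring date from last scan to last contact changes no d. It can add c ≥ 0 patients to the risk set, and 1 − d/(n + c) ≥ 1 − d/n. The estimate therefore rises or stays the same.

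**6. Size of the censoring effect.** A simulation used 20,000 patients, exponential progression times, the protocol's scan schedule, scanning that lapses independently of progression, and contact for 26 weeks beyond the lapse. All of these except the schedule are assumptions. The gain in 13-week Kaplan-Meier PFS from last-contact over last-scan censoring, in percentage points, was:

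| Stop scanning by week 13 | True 60% | True 70% | True 80% |
|---|---|---|---|
| 0% | 0 | 0 | 0 |
| 5% | 1.2 | 1.0 | 0.6 |
| 10% | 2.5 | 1.9 | 1.4 |
| 20% | 5.3 | 3.9 | 2.6 |

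**The case against.** The strongest reply is that the protocol leaves little room for these cases. Other anticancer therapy is barred until progression is documented, and patients who stop early are to be assessed until they progress. This stands as a limit on frequency. A reader who sees only the second Section 7.3 sentence might infer that any treatment is allowed once erlotinib stops. The sentence before it does not support that; together the two are ambiguous and need reconciling. The synopsis endpoint rule nevertheless foresees such patients, and no passage settles how to analyse them.

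The reach of last-contact censoring is also limited. It applies only to patients with neither progression nor death at the final analysis. A patient who misses scans and later has documented progression or dies is an event under either censoring date. Section 11.3 keeps the study open until every living patient has at least 6 months of follow-up after erlotinib, or all have died.

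The 12% and 24% could be misread as the trial's actual error rate. They are not. The hidden shares are hypothetical. The calculation concerns the binary count, and no passage says that count uses the Section 9.4 censoring date. Section 15 also offers the two-stage rule only as an alternative to the one-step Fleming design.

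A reader might further infer that the error always favours erlotinib. That holds for last-contact censoring, and for using Section 9.4 in place of the synopsis rule. It does not hold in general: under the synopsis rule the new-treatment error does not arise, and replacement has no fixed direction.

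**Conclusion.** The concern holds. The primary endpoint has conflicting event rules, with replacement as a third possible handling, and its progression component is censored at a date that gives no evidence on progression. The protocol fixes these rules itself, so this is not a detail merely left to a statistical analysis plan.

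The direction of the censoring effect is certain: upward or none. The size is not. It depends on how many patients miss scans while still in contact and how many start other treatment before progression, and it is zero if there are none of either. The assumed ranges above give 0.6 to 5.3 points on 13-week Kaplan-Meier PFS, and 12% or 24% against 5% for the two-stage rule. What needs no assumption about frequency is that, at the boundary, one patient's classification decides the outcome.

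It is tempting to go further and score every missing week-12 assessment as a failure. The protocol does not support that. It contains no such rule, it counts evaluable patients, and it gives no visit window, so a patient shown progression-free at weeks 6 and 18 would become a failure through one missed scan.

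**What to change.** Reconcile the synopsis (endpoint sentence and replacement provision), both definitions in Section 9.4, and Section 15 into one definition of PFS:

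- Event: RECIST progression, death from any cause, or start of other anticancer treatment before progression, as the synopsis already intends.
- Patients who start other treatment before progression are counted in the analysis and not replaced.
- Event-free patients are censored at the last adequate tumour assessment. Last contact stays as the censoring date for overall survival.
- PFS counting only RECIST progression and death is reported as a sensitivity analysis.

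The two Section 7.3 sentences on other therapy should also be reconciled; which clinical rule applies is for the investigators to decide.

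The cost is mainly wording plus one sensitivity analysis. One item needs checking first. Neither the schedule of assessments (Table 4) nor the recording list in Section 12.9 includes subsequent anticancer therapy or its start date, so it cannot be assumed that this date is collected. Confirm that the CRF records it, and add it if not. The downside is a slightly lower PFS estimate.
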